Additionally, there is very limited research examining the impact of quality of care received in a previous sector (e.g., an operating hospital before follow-up rehabilitation) on the quality and long-term outcomes of rehabilitation, even though many researchers (and lawmakers) have identified the need for German healthcare research to coordinate across sectors [20, 26, 27]. It does stand to reason that the treatment outcome of orthopedic rehabilitation after joint replacement hinges on the success of the previously performed surgery—patients that received surgery and postoperative care in a high-quality hospital are likely in better health at the start of follow-up rehabilitation (baseline). Thus, adjusting for risks in previous sectors (e.g., hospital quality, perioperative complications, pre-existing conditions) could likely improve the accuracy of quality assessment in subsequent sectors.

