### Data collection

#### Study part 1: prospective longitudinal study

Data for the prospective multicenter study will be collected over a period of approximately 7 months with paper-pencil questionnaires. Patient-reported outcomes are recorded at four time-points: in the beginning of rehabilitation (baseline; t0), completion of rehabilitation (t1), three-month follow-up after completion (t2), and six-month follow-up after completion (t3). T0 and t1 patient questionnaires are to be distributed to patients a maximum of 2 days after inpatient admission and a maximum of 2 days before discharge by the local study coordinator. Patient questionnaires for t2 and t3 (follow-ups) are sent to patients’ residential addresses with prepaid return envelopes. IRF medical staff are to record additional medical data in a case report form at baseline (t0) and at completion of rehabilitation (t1).

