### Study outcomes

#### Study 1: prospective longitudinal study

For study 1, the various outcomes and outcome domains are measured with different instruments and collected from different sources, as displayed in Table 2.

**Table 2 Tab2:** Outcomes, instruments, and data sources for study 1

Outcome (Domain)	Instrument	Data Source*	Time Point			
			t0	t1	t2	t3
Activities of daily living, emotional coping, mobility, physical functioning	Short Musculoskeletal Function Assessment (SMFA-D; [34])	P	x	x	x	x
Illness-related impairment/ “bother”	Short Musculoskeletal Impairment Assessment (SMFA-D; [34])	P	x	x	x	x
Physical pain	Visual Analogue Scale [35]	P	x	x	x	x
Pain-related self-efficacy	Pain Self-Efficacy Questionnaire (FESS; [36])	P	x	x	x	x
Walking ability	6 min Walk Test [37]	M	x	x		
Hip-specific outcome aspects such as limping, use of walkers, walking distance, climbing stairs, putting on shoes/socks	Harris Hip Score [38]	M	x	x		
Knee-specific outcome aspects such as mobility, stability	Knee Society Score [39]	M	x	x		
*Confounders*						
Comorbidity	Self-Administered Comorbidity Questionnaire (SCQ-D; [40])	P	x	x		
Age	Single item	P/M	x	x		
Gender	Single item	P/M	x	x		
Socio-economic status	Single item	P	x			
COVID-19-related stress	COVID-19 Stress Screening**	P	x			
Comorbidity	KOMO Score [41]	M	x			
Main and secondary diagnoses	ICD-10-GM codes [29]	M	x			

*P = patient-reported data, M = medical staff-reported data. **This instrument was developed by the principal investigator in 2020, publication is in progress. A translation of the adapted screening is attached in Additional File 1

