If at least two of the three validation criteria are met, the tested CD outcome variable is considered an adequate proxy for the respective PD outcome variable. Bland-Altman plots will be used for graphic evaluation of measurement differences [47, 48]. This same procedure will be applied to test H1b using CD quality indicators and PD quality indicators, which are represented by facility group mean values of PD outcome variables.

##### Hypothesis 2

H2 postulates an improvement in risk-adjustment models when considering cross-sectoral claims data, i.e., an increase in (adjusted) R^2^, and will be analyzed with nested multilevel regression models. A basic model (M0) will be estimated for each PD outcome variable using the PD confounders (see Table 2) on level 1. Models will be estimated for each time point after baseline (t1, t2, t3), and will be adjusted for *time* (rehabilitation effect) as a predictor on level 2. Furthermore, level 2 PD quality indicators will be included. Each model will be expanded with previously identified CD risk factors (on level 1 and level 2) as described in section “Study outcomes”. The nested models will be compared with Likelihood Ratio tests [49]. The analysis sample will be randomly divided into two parts, with one half allocated for analysis of risk-adjustment, and the remaining half used to validate the resulting models.

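### The H2 base model M0 leaves out each patient's t0 score of the outcome, so a claims factor that only repeats baseline status can count as an improvement

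*Protocol article*

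**What the plan says.** All references are to the protocol article.

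- **Data analysis and hypothesis testing, Hypothesis 2.** The comparator is fixed: "A basic model (M0) will be estimated for each PD outcome variable using the PD confounders (see Table 2) on level 1". On the occasions modelled: "Models will be estimated for each time point after baseline (t1, t2, t3"). The models are also adjusted for time, glossed as ("rehabilitation effect) as a predictor on level 2". On facility terms: "Furthermore, level 2 PD quality indicators will be included". These indicators are facility means of the outcome variables. CD risk factors are then added, improvement is read from adjusted R² and a likelihood ratio test, and half of the sample is kept for validation.
- **Study outcomes, Table 2.** The confounder block lists comorbidity ("Self-Administered Comorbidity Questionnaire (SCQ-D; [40"] and the KOMO score), age, gender, socio-economic status, COVID-19 stress and diagnoses. The seven outcome instruments stand above that block, and each is marked for t0.
- **Data collection.** "Patient-reported outcomes are recorded at four time-points: in the beginning of rehabilitation (baseline; t0").
- **Rehabilitation quality assurance in Germany.** On the effect of the preceding sector: "patients that received surgery and postoperative care in a high-quality hospital are likely in better health at the start of follow-up rehabilitation (baseline").

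Nowhere does the article say that the t0 score enters M0 as a covariate or that change scores are analysed.

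**The concern.** H2 is a relative claim, so its meaning depends on what M0 already knows. The t0 score is the most direct record of the patient's state on admission, and the study will hold it. The candidate CD risk factors named under Study outcomes (comorbidity, nursing care level, aspects of acute hospital care) are plausible markers of that same state, and the Background names baseline health as the route by which hospital quality acts.

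With t0 left out of M0, two situations look alike: a claims factor that tells the analyst something new, and one that only restates the t0 questionnaire or test. Both raise adjusted R² and both can win the likelihood ratio test. Random halving does not separate them, because the association of the stand-in with the outcome is real and recurs in the validation half. A positive H2 could then not be read as value added to the primary data already collected.

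This is a stated model choice, made by reference to a labelled block of Table 2. It is not a detail that an article would ordinarily leave to a fuller plan.

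**Working it through.** **1. Sample sizes from the plan (Sample size; Hypothesis 2).** Approached: 600 / (1 − 0.30) = 857.1, or 86 per facility × 10 = 860, as stated. Remaining after three follow-up points with 20% dropout each: 600 × 0.8³ = 307.2, a loss of 48.8%, which the plan rounds to 50% and n = 300. Half for model building: 300 / 2 = 150. The article gives no power, effect size or significance level for H2; 0.05 is assumed here.

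**2. Assumed inputs (not in the document).** Correlation of t0 with the later outcome: 0.5, range 0.4 to 0.6. Correlation of the claims factor with t0: 0.3, range 0.2 to 0.4. The claims factor carries no information beyond t0. Single-level model, no other covariates, one claims factor.

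**3. R² gain when t0 is omitted.** The claims factor then correlates with the outcome at 0.5 × 0.3 = 0.15, so the gain is 0.15² = 0.0225. With t0 in both models the true gain is 0.

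**4. Rejection by the likelihood ratio test.** Noncentrality = n × [−ln(1 − gain)], 1 degree of freedom.

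- n = 150: 150 × 0.02276 = 3.41, rejection 45.5%.
- n = 300: 300 × 0.02276 = 6.83, rejection 74.3%.
- Lower end, 0.4 and 0.2: gain 0.08² = 0.0064; rejection 17% (n = 150), 28% (n = 300).
- Upper end, 0.6 and 0.4: gain 0.24² = 0.0576; rejection 85% (n = 150), 99% (n = 300).

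**5. Simulation check.** 4000 runs per cell, linear models with four confounders, claims factor independent of those confounders, a wider range of assumed correlations.

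| t0–outcome, CD–t0 | n | Rejection without t0 | Adjusted R² gain without t0 | Rejection with t0 in both |
|---|---|---|---|---|
| 0.3, 0.2 | 150 | 12.4% | 0.004 | 6.0% |
| 0.5, 0.3 | 150 | 47.9% | 0.022 | 5.7% |
| 0.7, 0.5 | 150 | 99.6% | 0.121 | 5.3% |
| 0.3, 0.2 | 300 | 18.8% | 0.004 | 5.5% |
| 0.5, 0.3 | 300 | 74.8% | 0.022 | 5.6% |
| 0.7, 0.5 | 300 | 100% | 0.121 | 4.8% |

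With t0 in both models the mean adjusted R² gain was 0.000 in every cell.

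**6. Do the other M0 terms supply the baseline?** Facility means are not a patient's own t0 score, and time is not a baseline score either. In a model for one post-baseline occasion, time is constant and cannot act as a predictor. One coherent reading is therefore that t0 rows are kept as responses beside each follow-up. Even then t0 is not a covariate. In a two-occasion random-intercept model at n = 150, a claims factor acting only through t0 gave a significant test in 51% to 100% of runs (correlations 0.3 to 0.7 and 0.2 to 0.5).

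**7. Claims factors independent of t0.** At a t0–outcome correlation of 0.5, including t0 cuts residual variance by 0.5² = 25%, so the residual SD falls to √0.75 = 0.866, or 13% lower. Leaving t0 out makes such a factor harder to detect.

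**The case against.** The strongest reply is that H2, as worded under Hypotheses, compares a model with CD risk factors to one without them. A claims factor that tracks prior health does predict outcome. Against that wording, 46% is power to detect a real association. A reader might infer from the figures that the H2 test has an inflated type I error; the article does not support that, because the 5% benchmark belongs to a narrower question, namely added value beyond t0. The project also aims to reduce primary data collection (Practical implications), so a claims stand-in for a baseline survey has some interest. This stands, but it is a separate question. The Discussion speaks of improving the models used to judge facilities, and that calls for a comparator that uses the data already held.

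Other stronger readings also fail:

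- **The omission always favours claims data.** It does so only for factors that overlap with t0. For independent factors it costs precision.
- **M0 was made weak on purpose.** Nothing in the article shows intent.
- **Several confounders could be contaminated by t1 values.** Table 2 marks SCQ-D, age and gender at t1, but only SCQ-D could carry what happened during rehabilitation, and the article does not say that its t1 value will be used.
- **The joint is missing from M0.** Main diagnosis is already a confounder and largely identifies hip or knee.

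It is also fair that the time term leaves some doubt about how t0 is handled. Step 6 shows that this doubt does not remove the problem.

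**Conclusion.** The point holds in limited form. As specified, M0 has no t0 score of the outcome although the study collects it, and a claims factor that only repeats t0 information can pass the H2 criteria and the validation step. Under central assumptions the apparent R² gain is 0.0225, with rejection in about 46% (n = 150) or 74% (n = 300), against about 5% with t0 in both models.

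The size rests wholly on assumed correlations. The calculations ignore clustering in the ten facilities. Comorbidity, diagnoses, age and socio-economic status, already in M0, may absorb part of the overlap between claims factors and t0; neither the formula nor the simulation allows for that. For a factor that overlaps with t0, the direction does not depend on the values chosen. Nothing here shows that claims factors lack value beyond baseline; as planned, the analysis could not tell.

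**What to change.** - Include the t0 score of the same outcome in M0 and in every expanded model.
- Take SCQ-D at its t0 value.
- Test the CD risk factors over and above that model, and word H2 as added value beyond it.
- State how time enters models fitted for t1, t2 and t3, and whether t0 rows are ever responses.
- If claims data as a substitute for the baseline survey is also of interest, report the version without t0 as a separate, labelled question.

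The cost is a few sentences and no new data. The downside is that the reported gain from CD risk factors may be smaller.

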### Study population and recruitment

#### Study 1: prospective longitudinal study

For study 1, ten German inpatient rehabilitation facilities (IRFs) were enlisted in the study by local representatives of the regional AOK health insurance funds, which in turn are recruiting a planned sample of 600 patients. Participating IRFs signed a collaboration agreement with the principal investigator, and each appointed a local study coordinator in charge of organization and implementation of all project tasks (e.g., recruitment of participants, distribution of patient information and consent forms, storing/safekeeping signed consent forms). Patient recruitment began in November of 2022 and will end in December 2023.

Patients eligible for participation are recruited on-site in the beginning of their orthopedic follow-up rehabilitation. Study coordinators present them with a physical copy of the study fact sheet (covering study synopsis, data protection, and other legal aspects), and ask for their participation. Those agreeing to participate sign an informed consent form. Eligibility is determined by meeting the inclusion criteria: Participants must be at least 18 years old at time of inclusion (beginning of rehabilitation), insured through AOK health insurance fund (for purposes of data availability), and receive inpatient orthopedic follow-up rehabilitation after implantation of a knee joint replacement or hip joint replacement due to osteoarthritis. Participants need to demonstrate sufficient knowledge of the German language and sufficient cognitive abilities to answer the comprehensive questionnaires independently. Patients that prematurely discontinue rehabilitation, demonstrate insufficient German or cognitive skills, or change health insurance within the study period will be excluded.

Participation in the study is incentivized with a €50 gift voucher for patients that complete all four questionnaires, while IRFs receive €120 per patient for full patient participation and completed case report forms.

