### Sample size

#### Study 1: prospective longitudinal study

Recruiting IRFs are encouraged to assess every patient for eligibility (as per the inclusion criteria), with a target sample of 60 participants per facility totaling *N* = 600 cases. Assuming an initial refusal quota of 30% (non-response), IRFs need to approach 860 patients, or 86 patients per facility. Withdrawal of consent or loss to follow-up throughout the data collection phase are estimated to result in an average dropout rate of 20% for each time point, which will reduce the initial target sample by approximately 50%. Thus, we expect a sample of n = 300 to remain for analysis (comparable studies report dropout rates of 25–55%, depending on the length of observational period; [31–33]). Figure 2 visualizes the sample flow in a CONSORT flow diagram.

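### Hypothesis 2: with ten facilities, the usual chi-square reference for the likelihood-ratio test does not hold for claims factors that are constant within a facility

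*Protocol article*

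**What the plan says.** Under Study population and recruitment, Study 1, the article reports that "ten German inpatient rehabilitation facilities (IRFs) were enlisted in the study". Under Sample size, recruitment is planned "with a target sample of 60 participants per facility totaling" 600, with an "average dropout rate of 20% for each time point", "which will reduce the initial target sample by approximately 50" per cent, leaving 300 for analysis.

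Under Data analysis and hypothesis testing, Hypothesis 2, a basic model for each PD outcome holds the PD confounders on level 1. The text then adds: "Furthermore, level 2 PD quality indicators will be included". The section on Hypothesis 1 represents these indicators by facility group means of the PD outcomes. The next step is: "Each model will be expanded with previously identified CD risk factors (on level 1 and level 2"). The comparison is by likelihood ratio: "The nested models will be compared with Likelihood Ratio tests [49"]. One random half of the analysis sample is used to build the models and the other half to validate them.

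The article names no small-sample reference for this test. It gives no significance level for it, no ICC, and no number of level-2 terms.

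**The concern.** A factor that takes one value per IRF is informed by ten facility values, however many patients each IRF contributes. The chi-square reference for the likelihood-ratio (LR) statistic is a large-sample result, and for such a factor the relevant sample is the number of facilities. Maximum likelihood (ML) also estimates the between-facility variance without deducting the level-2 terms already fitted. Each PD indicator in the model uses one of nine between-facility degrees of freedom before any CD factor is tested. When the facility variance is not negligible, it is underestimated and the statistic is too large.

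H2 concerns risk factors on both patient and facility levels, and models are fitted for each PD outcome at t1, t2 and t3. At stake is whether the facility-level part of H2 could appear confirmed through chance differences among ten IRFs.

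**Working it through.** **The plan's own figure.** Three losses of 20%: 600 × 0.8³ = 600 × 0.512 = 307, against the stated 300. Per IRF: 300 / 10 = 30. After the random halving: 30 / 2 = 15 patients per IRF in the model-building half.

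**Inputs from the article.** J = 10 IRFs; 15 patients per IRF, as just derived; CD factors on level 2; PD quality indicators on level 2; LR tests.

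**Assumptions, because the article gives no values.** Level 5%; ICC 0 to 0.10; p = 0, 3 or 6 level-2 PD indicators, none of them the modelled outcome's own facility mean; k = 1 or 2 added CD factors, constant within IRF and without effect; balanced random-intercept model fitted by ML.

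**Limit in closed form.** When the between-facility variance is estimated above zero, LR = 10 × ln(RSS0/RSS1), where RSS0 and RSS1 are the between-facility residual sums of squares without and with the k factors. With c the 95% point of chi-square(k), LR > c is the same event as

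F > (exp(c/10) − 1) × (9 − p − k)/k, with F on (k, 9 − p − k) degrees of freedom.

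- p = 0, k = 1: c = 3.841, exp(0.3841) − 1 = 0.468, and 0.468 × 8 = 3.75. P(F(1, 8) > 3.75) = 8.9%.
- p = 3, k = 2: c = 5.991, exp(0.5991) − 1 = 0.8205, and 0.8205 × 4/2 = 1.64. P(F(2, 4) > 1.64) = (1 + 0.8205)^(−2) = 30.2%.

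These are limits for a clearly positive facility variance. At small ICC the variance is often estimated as zero and the rate is lower, so simulation is needed.

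**Simulated null rejection rate of the nominal 5% LR test** (10 IRFs, 15 per IRF, 400,000 replicates per cell):

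| PD indicators p | CD factors k | ICC 0.02 | ICC 0.05 | ICC 0.10 |
|---|---|---|---|---|
| 0 | 1 | 5.7% | 7.2% | 8.4% |
| 3 | 2 | 9.3% | 14.9% | 21.5% |
| 6 | 2 | 11.2% | 19.7% | 32.6% |

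At ICC 0 the rate is about 4% to 6%, depending on p and k. An F test on (k, 9 − p − k) degrees of freedom, applied to the same draws, gives about 5% in every cell.

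**Is the number of facilities the cause?** With p = 2, k = 2, ICC 0.05 and 15 patients per unit, the rate is about 13% with 10 units and about 7% with 50.

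**Two cases in which the inflation does not appear.**
- If the modelled outcome's own facility mean is in the comparison model, it absorbs the between-facility variance. The LR test for an added facility factor then rejects in 0% (mean from the same half) or 0.2% to 0.8% (mean from the full sample).
- At ICC 0.05 with one added factor, a factor varying only within IRFs has a rate of 4.9%, and one varying half within and half between IRFs has 6.5% (1,500 replicates).

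**The case against.** The strongest objection is that the one facility-level factor the article names is the quality of the operating hospital (Study outcomes, Study 2; Data analysis, Study part 2; Discussion). Patients in one IRF can come from different hospitals, so such a factor varies within IRFs and the ten-facility argument largely falls away. This stands, and it limits the point to factors constant within an IRF. It does not remove the point, because Hypothesis 2 adds CD factors on level 2 in models whose level-2 PD indicators are IRF means.

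Second, the ICC, the significance level and the numbers of level-2 terms are all assumed, and the high rates need several level-2 terms and an ICC of 0.05 or more. This stands too. A reader might infer that useless facility factors will be declared improvements at several times 5%. The article does not support that as a general statement: with one factor and no PD indicators the excess stays below twofold (limit 8.9%), at ICC 0 there is little or none, and with the outcome's own mean in the model the error runs the other way. Adding level-1 factors to a joint test also dilutes the excess.

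Third, a condensed article may leave the reference distribution to an analysis plan, and a bootstrap LR test would be compatible with its sentence. That is fair, but the method is stated as a plain LR test for both levels, and its usual reference is chi-square.

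Fourth, H2 also looks at adjusted R² and uses a validation half. A reader might infer that validation cannot expose a false positive. The article does not say how the random split treats facilities. If it is by patient within the same ten IRFs, both halves share the facility effects and validation is a weak safeguard, not a useless one.

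**Conclusion.** The concern holds in limited form. For CD factors constant within an IRF, the chi-square LR test does not keep its level with ten facilities. Without the outcome's own facility mean in the model, the excess over 5% ranges from negligible (ICC near 0) through modest (one factor, no PD indicators) to substantial (two factors, 3 to 6 PD indicators, ICC 0.05 to 0.10). With that mean in the model, the test can hardly reject at all. On neither reading can 5% be relied on. The sizes rest on the assumed level, ICC, numbers of level-2 terms, and a balanced random-intercept model with 15 patients per IRF. Level-1 factors that vary within IRFs, and operating-hospital quality so far as it does, are little affected.

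**What to change.** - Test level-1 CD factors and IRF-constant level-2 CD factors separately.
- For the IRF-constant factors, use REML with Kenward-Roger or Satterthwaite F tests, or a parametric-bootstrap LR test that simulates the ten-IRF structure.
- Keep the chi-square LR test for factors that vary within IRFs.
- State which facility means enter the comparison model, and in particular whether the modelled outcome's own mean is among them.
- No fixed cap on level-2 terms is needed, but their number must leave enough of the nine between-facility degrees of freedom for the test.

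The cost is analysis-plan wording and standard software options, with no new data. The downside is lower apparent power for facility-level factors, which reflects how little ten facilities can show about them.

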## Study design and methods

SEQUAR combines two studies in one project: A prospective longitudinal multicenter study collecting patient- and health professional-reported data (study 1), and a retrospective cohort study using health claims data (study 2).

In study 1, patients in orthopedic follow-up rehabilitation after hip or knee arthroplasty and their physicians are repeatedly surveyed with a set of validated instruments at different phases throughout their post-op treatment. The instruments used allow comprehensive assessment of the various (long-term) outcome domains of rehabilitation (PD outcome variables), and are the current best-practice assessment against which the claims data outcomes (CD outcomes) will be tested (see section “Study outcomes”). Facility-level quality indicators based on primary data (PD quality indicators) will be calculated for individual facilities by grouped scale means.

For study 2, health claims data (CD) will be extracted from the AOK health insurance fund database (see section “Sample”). Participants of study 1 are a small subsample of the larger study 2 sample. The large study 2 sample will be used to explore, identify and validate potential CD outcome variables, CD quality indicators, and CD risk factors. The subsample of claims data from study 1 participants will be matched to the outcome variables in the PD dataset resulting from study 1, and split into two subsamples for analysis and validation, respectively. Figure 1 illustrates the data flow.

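### The H2 risk-adjustment models are fitted on a random half of the sample (about 150 of 300 at t3), which costs power and probably does not test transfer to other facilities

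*Protocol article*

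**What the plan says.** For study 1, "ten German inpatient rehabilitation facilities (IRFs) were enlisted in the study", "with a target sample of 60 participants per facility totaling" 600. The sample size section assumes an "average dropout rate of 20% for each time point, which will reduce the initial target sample by approximately 50" per cent, and concludes: "Thus, we expect a sample of n = 300 to remain for analysis".

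H2 compares a basic model (M0, primary-data confounders) with models expanded by claims-data risk factors on patient and facility level. The criteria are the gain in (adjusted) R-squared and likelihood ratio tests, at t1, t2 and t3 separately. The section ends with the split: "The analysis sample will be randomly divided into two parts, with one half allocated for analysis of risk-adjustment", the other half being kept for validation. The section Study design and methods announces the same for the matched study 1 data, which are to be "split into two subsamples for analysis and validation, respectively".

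The article describes no resampling, no split by facility and no validation in other facilities for H2. It gives no effect size, alpha or number of added risk factors for H2.

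**The concern.** A single random half-split is an expensive form of validation at this sample size. The estimates and tests that decide H2 use half the patients, so a real improvement in risk adjustment is more likely to be missed. The result also depends on one draw among many equally valid ones.

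The purchase is limited as well. The project aims at a quality assurance procedure for orthopedic rehabilitation in general, so it matters how the models behave in facilities that did not contribute to fitting. A split by patient leaves every facility in both halves and cannot show this.

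**Working it through.** **1. The article's own figures.** Approached: 600 / 0.70 = 857, stated as 860, or 86 per facility. Remaining: 600 × 0.8³ = 307, stated as about half, i.e. 300. Both reproduce.

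**2. Patients left to fit H2.** The dropout rate of 20% is applied once per post-baseline time point; ten facilities.

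| Time point | Expected | Half | Half, per facility |
|---|---|---|---|
| t1 | 600 × 0.8 = 480 | 240 | 24 |
| t2 | 600 × 0.8² = 384 | 192 | 19 |
| t3 | 300 (stated; 307 computed) | 150 | 15 |

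**3. Standard errors.** For a patient-level coefficient the ratio is √(300/150) = √2 = 1.41, a rise of 41%. A facility mean based on m patients has variance proportional to ICC + (1 − ICC)/m. Going from m = 30 to m = 15, with assumed ICCs:
- ICC 0.02: √(0.0853/0.0527) = 1.27
- ICC 0.05: √(0.1133/0.0817) = 1.18
- ICC 0.10: √(0.160/0.130) = 1.11

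Facility-level quantities therefore lose about 11% to 27% in precision, less than patient-level ones.

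**4. Power of the likelihood ratio test.** The article gives no inputs, so these are assumptions: five added factors, base R² = 0.20, alpha 0.05, clustering ignored. Noncentrality = n·ΔR²/(1 − R² − ΔR²), chi-square with 5 degrees of freedom (critical value 11.07). For ΔR² = 0.03 at n = 150: 150 × 0.03/0.77 = 5.84.

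| Time point | Half: n, power | All: n, power |
|---|---|---|
| t1 | 240, 64.3% | 480, 93.7% |
| t2 | 192, 53.2% | 384, 86.5% |
| t3 | 150, 42.2% | 300, 75.6% |

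For ΔR² = 0.05 at t3 the pair is 68% against 95%.

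**5. Sensitivity at t3 (150 against 300).** A noncentral F test with 8 base predictors gives:

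| Added factors | ΔR² 0.03 | ΔR² 0.05 | ΔR² 0.08 |
|---|---|---|---|
| 3 | 49% / 82% | 75% / 97% | 94% / 100% |
| 5 | 41% / 75% | 66% / 95% | 89% / 100% |
| 10 | 29% / 61% | 51% / 88% | 78% / 99% |

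The loss is about 22 to 37 points for gains of 0.03 to 0.05, and about 6 to 21 points for 0.08. With the chi-square formula, five factors and ΔR² = 0.03, moving the base R² to 0.10 or 0.40 gives 37.5% against 69.5%, or 55.8% against 88.6%.

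**6. Facilities in each half.** In 20,000 simulated random splits of 300 patients over ten equal facilities, every facility appeared in both halves every time. The smallest and largest facility counts in one half averaged about 11 and 19.

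**The case against.** The strongest reply is that a half-split is a conventional and honest validation: the held-out patients are different people, so overfitting will show. That stands. A reader might infer that H2 has no independent validation at all, but the split does supply an internal check. What it lacks is independence from the facilities, and only if the split is by patient. The unit is not stated. By patient is the natural reading; a split by facility would leave five facilities per half. The article does not claim transfer to new facilities here, and its limitations section discloses that the facilities were pre-selected.

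Other stronger readings also go too far:
- **That all H2 models rest on 150 patients.** This is the t3 figure. The 6-minute walk, Harris Hip and Knee Society scores are collected only at t0 and t1, and multiple imputation, if the missingness analysis supports it, may keep more patients.
- **That 150 contradicts the stated 300.** The article expects 300 for analysis and then divides that sample. The two statements are compatible.
- **That a split is unnecessary because the risk factors come from a separate cohort of about 312,000.** Study 1 participants are a subsample of that cohort, and the claims data hold no primary-data outcomes. Coefficients for those outcomes are estimated in study 1, so optimism remains and must be corrected.
- **That spurious R-squared from the parameter count would by itself carry H2.** The plan uses (adjusted) R-squared and likelihood ratio tests, both of which account for the number of parameters.

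Finally, the power figures rest on inputs the article does not give. The direction and the √2 for patient-level terms do not depend on them; the percentages do.

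**Conclusion.** The point holds as a matter of efficiency and of what the validation can show. The stated split halves the data for fitting and testing H2 at every time point. Under the assumed inputs, with gains of 3 to 5 points of R-squared, this costs roughly a quarter to a third of the attainable power in absolute terms at t3. For larger gains the loss is smaller. Resampling can correct optimism without that cost.

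Neither approach changes the number of facility-level units: there are ten with or without the split, so facility-level risk factors remain weakly informed. The change is worth making before analysis, but the plan as written is inefficient rather than invalid.

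**What to change.** In the section Hypothesis 2, replace the half-split sentence with three steps:
1. Fit and compare M0 and the expanded models on all available patients at each time point.
2. Report R-squared corrected for optimism by bootstrap, repeating all modelling steps in each resample.
3. Add leave-one-facility-out validation, with a note that ten pre-selected facilities limit what it can show about others.

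In the section Study design and methods, change the sentence on the two subsamples only as far as it concerns H2. That sentence covers the matched dataset used for all hypotheses, and nothing here argues for changing H1a or H1b.

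The cost is more computing, a wording change and the loss of a single untouched hold-out set. No new data are needed.
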